## Abstract

Cultural beliefs, personal experiences, and historic abuses within the healthcare system—rooted in structural racism—all contribute to community distrust in science and medicine. This lack of trust, particularly within underserved communities, contributes to decreased participation in clinical trials and a lack of representation in the data. Open dialogue about community concerns and experiences related to research participation and medical care processes can help build trust and change attitudes and behaviors that affect community health. This protocol outlines an approach to increase trust in science and clinical trials among communities in the Bronx, New York that are typically underrepresented in research data. Bridging Research, Accurate Information and Dialogue (BRAID) is a two-phased, evidence-based community engagement model that creates safe spaces for bilateral dialogues between trusted community messengers, and clinicians and scientists. The team will conduct a series of BRAID Conversation Circles on the topic of clinical trials with local trusted community messengers. Participants will be members of the community who are perceived as “trusted messengers” and can represent the community’s voice because they have insight into “what matters” locally. Conversation Circles will be audiotaped, transcribed, and analyzed to identify emergent challenges and opportunities surrounding clinical trial participation. These key themes will subsequently inform the codesign and co-creation of tailored messages and outreach efforts that community participants can disseminate downstream to their social networks. Surveys will be administered to all participants before and after each Conversation Circle to understand participants experience and evaluate changes in knowledge and attitudes about clinical trials, including protections for research participants the advantages of having diverse representation. Changes in motivation and readiness to share accurate clinical trial information downstream will also be assessed. Lastly, we will measure participants dissemination of codesigned science messages through their social networks by tracking participant specific resource URLs of materials and videos posted on a BRAID website. This protocol will assess the effectiveness and adoptability of an innovative CBPR model that can be applied to a wide range of public health issues and has the potential to navigate the ever-changing needs of the communities that surround health systems.

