Since communities shift over time and can vary greatly among each other, using a community-based engagement model to elicit rapid input on perceptions, doubts, and knowledge gaps poses a promising way to strengthen trust and determine best practices for working with individual communities. To narrow the gap of existing health disparities, distrust in scientific research and healthcare delivery systems must be addressed. The creation of safe spaces for open, bidirectional conversations, where communities can share their experiences and expectations, can help rebuild and nurture trust, and form a foundational infrastructure to meaningfully move toward health equity (13).

Montefiore/Einstein is the largest healthcare provider in the Bronx, New York. The borough is home to a large community of color, with 44 and 57% of the population identifying as Black or African American, and Hispanic or Latino, respectively (14). To build trust in science, medicine, and research (e.g., clinical trials) in the Bronx communities, our research team will employ the Bridging Research, Accurate Information and Dialogue (BRAID) model to engage trusted community messengers from the Bronx in a series of ongoing dynamic dialogues called Conversation Circles (15–19).

We anticipate that within these safe spaces, community concerns related to trust in research, science, healthcare, structural racism, and health disparities will emerge, and gaps in knowledge and misinformation can be identified and filled. As accurate information is shared within the circles, our team will facilitate codesign processes to support the coproduction of accurate scientific messages tailored to the local community. We predict that participation in BRAID will enhance community confidence and trust in science and clinical trials, as well as increase trusted community messenger motivation and self-efficacy to disseminate accurate information (co-created messages) through their social networks.

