#### BRAID Conversation Circles (step 2)

2.2.2

Once trusted messengers are identified, we will invite them to participate in a series of dynamic BRAID “Conversation Circles.” During these dialogues, a motivational interviewing (MI) aligned facilitation style will be employed to elicit important community perspectives, understand “*what matters*” most to the community, and create a space where clinical and scientific experts are invited to share accurate information that addresses community concerns (23). We envision that themes related to trust in research, science, healthcare, structural racism, and health disparities will emerge, and that gaps in knowledge and misinformation will be identified. Further, Conversation Circles will be similarly used to obtain community feedback and sentiment on published research findings directly relevant to members in their community. Throughout the Conversation Circle process, a facilitator will guide the participants towards critically reviewing learned information and codesigning solutions and accurate messages that they deem appropriate to share with their community networks.

We will implement up to 15 unique Conversation Circle cohorts. Four to 12 trusted community messengers will participate in each cohort, and clinical and scientistic guests will be selected and invited to attend and contribute to the dialogue based on their ability to address emerging community concerns. Each Conversation Circle will meet 1–5 times with 1–3 weeks between each circle. Conversation Circles will take place in-person or virtually using Zoom and will be recorded and transcribed. Surveys will be collected before and after each Conversation Circle to understand participant experience and confidence in knowledge of accurate information, assess participant perception of the information shared (i.e., the benefit of having diversity in clinical trials, protections in place to protect study participants, relevant study findings), and explore participant desire and self-efficacy to share accurate information downstream to their community (Appendix C).

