### Data analysis plan

2.5

BRAID is a mixed-methods study. Key quotes and themes from the transcriptions of the audio or video-recorded Conversation Circles will be identified via inductive thematic analysis based on a codebook that will be developed by the BRAID research team. At least 2 BRAID research team members will independently code each Conversation Circle transcript using Dedoose qualitative analytics software. Following initial Conversation Circle transcript coding, the BRAID team will collectively assess inter-coder reliability and alignment of transcript coding to the established code book categories. Network analysis will be conducted using data collected from the “Getting Ready to BRAID” interview responses to identify associations between BRAIDer responses and successful BRAIDing. Descriptive statistics and quantitative data from both pre- and post-Conversation Circle survey responses will be analyzed using SPSS and/or R. All data will be analyzed using grounded theory methods (25, 26). Google campaign analytics will be used to track the reach of each BRAIDer’s message dissemination through social media.

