Our study has several limitations. First, recruitment bias may be introduced because our CBO partners will be responsible for identifying potential Community Experts rather than community members volunteering themselves or being selecting by the BRAID research team. We attempted to minimize this bias by creating clear guiding principles for objectively identifying BRAID participants which will be shared with our CBO partners and included in our BRAID manual. Our protocol is also potentially subjective to social desirability bias. While it is important to recognize that the goal of BRAID Conversation Circles is to provide a space for bidirectional dialogues that may influence or altogether change the attitudes and beliefs of participants, we will distribute pre- and post-surveys outside of the Conversation Circle group setting to minimize this risk. As the process of engaging with participants who do not complete their series of Conversation Circles is not included in the current protocol, potential for attrition bias also exists. Lastly, we acknowledge that our study findings may not be clearly generalizable to communities different than the ones included within the Conversation Circles. Nevertheless, the BRAID model can be adapted to address a broad range of public health concerns regardless of community demographics.

BRAID has the potential to serve as a foundational infrastructure for a Learning Health Care Community (27, 28). In this paradigm, a robust network of “BRAIDers” who trust science and the healthcare system, could be leveraged by an anchor institution to provide ongoing local community input into health equity programming, research design, and dissemination. This kind of long-term investment can further cultivate meaningful community partnerships and collaborations that address the underlying structural factors that drive health disparities, in order to achieve health equity.

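### The abstract promises an assessment of effectiveness, but every cohort receives BRAID, survey change is only before versus after, and the missing comparator is not listed as a limitation

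*Protocol article*

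**What the plan says.** The aim is in the closing sentence of the Abstract: "This protocol will assess the effectiveness and adoptability of an innovative CBPR model". The Introduction (section 1) gives a directional prediction: "We predict that participation in BRAID will enhance community confidence and trust in science and clinical trials".

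The data behind these statements are described as follows.

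- **Surveys.** "Surveys will be administered to all participants before and after each Conversation Circle" (Abstract).
- **Cohorts.** "We will implement up to 15 unique Conversation Circle cohorts", and "Four to 12 trusted community messengers will participate in each cohort" (section 2.2.2).
- **Sessions.** "Each Conversation Circle will meet 1–5 times with 1–3 weeks between each circle" (section 2.2.2).
- **Quantitative analysis.** "Descriptive statistics and quantitative data from both pre- and post-Conversation Circle survey responses will be analyzed using SPSS and/or R" (section 2.5).
- **Other sources.** Two exit interviews per BRAIDer (2.3.2), website traffic by BRAIDer code (2.3.3), a focus group (2.4), and thematic coding of transcripts (2.5).

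The Discussion (section 3) names four limitations: recruitment through partner organisations, social desirability, attrition and generalisability. Against social desirability it offers a mitigation: "we will distribute pre- and post-surveys outside of the Conversation Circle group setting to minimize this risk".

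**The concern.** Effectiveness, and a predicted rise in trust brought about by participation, are causal ideas. They need some account of what would have happened without BRAID. The text describes no control, wait-list, staggered start or repeated survey before exposure.

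The rival explanations are concrete here. Participants are paid and, after each session, are asked about the information just shared. In cohorts that meet more than once they answer surveys repeatedly. A five-meeting series has four gaps of 1–3 weeks and so spans 4 to 12 weeks, during which outside events can move opinion.

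At stake is what the study may conclude. The Discussion envisages extending the model to vaccination, food insecurity, mental healthcare and cancer prevention. A pre-post rise reported as effectiveness could be used to support that extension without the evidence the word implies.

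**Working it through.** The article states no sample size target, power, alpha or effect size, so there is no figure to reproduce. The main check is textual.

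**Step 1. Does any data source carry a comparison that could support an effect claim?**

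| Source | Section | Unexposed comparison described? | What it can show |
|---|---|---|---|
| Pre/post surveys | Abstract, 2.2.2, 2.5 | None; all participants are exposed | Change among participants |
| Exit interviews and network analysis | 2.3.2, 2.5 | None; BRAIDers compared with each other | Readiness, experience, correlates of sharing |
| Link traffic by code | 2.3.3 | None; no value before exposure | Reach |
| Focus group | 2.4 | None | Experience |
| Thematic analysis | 2.5 | None | Themes and concerns |

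**Step 2. How many surveys precede exposure?** With 1 to 5 meetings, a participant completes 2 to 10 surveys (2 × 1 to 2 × 5). Only the survey before the first meeting is unexposed. A one-meeting cohort has one pre and one post. With a single unexposed time point, a trend or testing effect cannot be estimated before BRAID begins.

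**Step 3. Is the gap disclosed?** Social desirability and selection by partner organisations are disclosed. The missing comparator, testing effects and time trends are not.

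**Step 4. Illustration of size, under assumptions.** Inputs from section 2.2.2: 15 cohorts of 4, 8 (midpoint) or 12 give n = 60, 120 or 180. Assumptions not in the article: all 15 cohorts run, pre/post correlation 0.5, participants independent within cohorts, a two-sided 5% test, and a true BRAID effect of zero with an artefactual shift b in SD units.

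SE = sqrt(2 × (1 − 0.5)) / sqrt(n) = 1 / sqrt(n)

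P(significant and favourable) = Phi(b × sqrt(n) − 1.96)

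Example: b = 0.2, n = 60 gives Phi(0.2 × 7.746 − 1.96) = Phi(−0.411) = 0.34.

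| Assumed shift b | n = 60 | n = 120 | n = 180 |
|---|---|---|---|
| 0 | 0.025 | 0.025 | 0.025 |
| 0.1 SD | 0.12 | 0.19 | 0.27 |
| 0.2 SD | 0.34 | 0.59 | 0.77 |
| 0.3 SD | 0.64 | 0.91 | 0.98 |

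The useful message is the direction: recruiting more participants makes a false attribution more likely, so sample size does not cure the problem.

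**The case against.** Several counter-arguments have force.

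- **Part of the problem is already disclosed.** The Discussion admits social desirability and nomination by partner organisations, and offers a mitigation for each. A reader might infer that the plan overlooks reporting bias; it does not. Distributing surveys outside the group may reduce that bias, but it can neither measure nor remove it.
- **The study is more than a pre/post survey.** It is mixed-methods, it relates BRAIDer responses to successful sharing, and link traffic is not self-report. Section 2.3.2 also uses effectiveness for how well BRAIDers share information, so the abstract's word need not refer to survey scores alone. This stands as a limit on the criticism, but none of these sources supplies a comparison without BRAID, and the Introduction's prediction does concern trust.
- **The article reaches no conclusion.** A reader might infer that any rise will be counted as effect. The article states no effect estimate or decision rule, and the Discussion is hedged. The defect lies in the stated aim and the incomplete limitations, not in a declared inference.
- **The probabilities are not specific to BRAID.** In any one-group study a nonzero bias becomes significant as n grows. The shifts are assumed, the article names no test, clustering within discussion cohorts is ignored, and the number of cohorts is a maximum, so 60 is not a floor. All of this stands.
- **Surveys already bracket each circle.** In cohorts with several meetings, the interval from one post-survey to the next pre-survey shows change without a session. But those participants are already exposed, so it is not an untreated interval.

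A condensed article may leave analytic detail to other documents. That does not answer this point, because the article states both aim and design, and an analysis plan cannot supply a comparator that the design lacks. Figure 3 (study design) was not available for this check; no text suggests that it shows a comparison group.

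**Conclusion.** The point holds in a limited form. The stated aim claims a property that the described design lacks, and the limitations do not tell the reader so. The study can describe pre-post change among participating Community Experts, along with adoptability, experience and reach. It cannot attribute a change in trust or knowledge to BRAID.

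This rests on the article's text. The probabilities in the working are illustrative and the conclusion does not depend on them. They should not be read as the study's false-positive rate. Nor does the point invalidate the descriptive, qualitative or feasibility work, which needs no comparator.

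**What to change.** **Main change (wording only).** Restate the aim in the Abstract as describing pre-post change among participating Community Experts, together with the adoptability and reach of dissemination, and align the Introduction's prediction with it. In the Discussion, add the missing comparator, testing effects and time trends to the limitations, so that a pre-post rise is not reported as effectiveness. The cost is a few sentences and a more modest headline claim.

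**Optional addition.** Send the same pre-survey at invitation as well as before the first meeting, and report the change over that untreated interval beside the change over BRAID. It costs one extra short survey per participant and slight burden. It is a partial check on testing and time trend only. It does not address a reporting shift caused by attending the sessions, and the invitation interval may differ in length from the BRAID interval, so it should not be called an internal control. It supplements the wording change and does not replace it.

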
## Introduction

1

In order to meaningfully engage communities to co-create and implement strategies to achieve health equity and combat misinformation, anchor institutions need to first earn trust. Many health disparities are rooted in historic structural racism (1, 2). Repeated injustices, including a legacy of research abuses and medical exploitation of underserved communities, have reinforced distrust in medicine and research within communities of color (3, 4).

To date, individuals in the United States identifying as Black or Latino represent 15 and 13% of those affected by cancer, respectively, yet only comprise 4–6% and 3–6% of those enrolled in clinical trials (5). Since the onset of the COVID-19 pandemic, barriers to the participation of underrepresented populations in research have persisted, potentially deepening healthcare inequities and limiting patient access to precision medicine (6–8). Though the 1993 National Institutes of Health Revitalization Act mandated an increase in the enrollment of women and underrepresented ethnic groups in clinical trials, efforts to combat underrepresentation by research teams have had limited success (9, 10). Therefore, there has been a continued and evolving effort by the National Institutes of Health to increase the participation of underrepresented populations in clinical trial research.

A systematic review of published interventions aiming to increase the participation of underrepresented populations in cancer clinical trials described efforts ranging from patient navigators, culturally-tailored informational videos, research team competence training, and relationship building/social marketing (5). While many of the efforts demonstrated favorable increases in enrollment of underrepresented populations, it is difficult to conclude that one particular approach is most impactful, as achieving diversity in clinical trials is a multifaceted issue. However, research has consistently demonstrated that trust and a feeling of partnership with members of the medical community are key influencers of patient willingness to participate in clinical trials (4, 11, 12).

Since communities shift over time and can vary greatly among each other, using a community-based engagement model to elicit rapid input on perceptions, doubts, and knowledge gaps poses a promising way to strengthen trust and determine best practices for working with individual communities. To narrow the gap of existing health disparities, distrust in scientific research and healthcare delivery systems must be addressed. The creation of safe spaces for open, bidirectional conversations, where communities can share their experiences and expectations, can help rebuild and nurture trust, and form a foundational infrastructure to meaningfully move toward health equity (13).

Montefiore/Einstein is the largest healthcare provider in the Bronx, New York. The borough is home to a large community of color, with 44 and 57% of the population identifying as Black or African American, and Hispanic or Latino, respectively (14). To build trust in science, medicine, and research (e.g., clinical trials) in the Bronx communities, our research team will employ the Bridging Research, Accurate Information and Dialogue (BRAID) model to engage trusted community messengers from the Bronx in a series of ongoing dynamic dialogues called Conversation Circles (15–19).

We anticipate that within these safe spaces, community concerns related to trust in research, science, healthcare, structural racism, and health disparities will emerge, and gaps in knowledge and misinformation can be identified and filled. As accurate information is shared within the circles, our team will facilitate codesign processes to support the coproduction of accurate scientific messages tailored to the local community. We predict that participation in BRAID will enhance community confidence and trust in science and clinical trials, as well as increase trusted community messenger motivation and self-efficacy to disseminate accurate information (co-created messages) through their social networks.

## Methods and analysis

2

### The BRAID model

2.1

BRAID is an evidence-based, iterative, biphasic community engagement model developed by author [name] and researchers at the Albert Einstein College of Medicine (15–19). The model closely aligns with the Association of American Medical Colleges Principles of Trustworthiness (13, 15) and is summarized in Figure 1.

**Figure 1 fig1:**
[figure not shown]
The bridging research, accurate information and dialogue (BRAID) model.

During Phase 1 of the BRAID model, safe spaces (“Conversation Circles”) are created for ongoing dialogues between “trusted community messengers” (“Community Experts”) and clinicians and scientists representing public health and/or health systems. Once a sense of trust is established, participants are supported as they work together to co-create accurate health messages tailored for the local community. In Phase 2 of the model, trusted messengers are empowered to disseminate co-created messages through their social networks. The process of sharing information is called “BRAIDing” and the trusted community messengers who share information are called “BRAIDers.” BRAIDers bring lessons learned about emerging community concerns and beliefs (i.e., conspiracy theories, misinformation) back to the Conversation Circles to inform the development of new health messages that address *what matters* to their community. This iterative approach moves community members along the spectrum of public participation (Figure 2). A glossary of key Conversation Circle terms can be found in Appendix A and a BRAID implementation toolkit including guidance for implementing BRAID with fidelity is in development.

